### 2.9. Secondary Outcomes

Based on the diary (Figure 2), the changes in the percentage of volunteers with a weekly mean frequency of CSBMs ≥3 [32, 54, 55], changes in the weekly mean frequency of spontaneous bowl movements (SBMs) [32, 54–56], weekly mean stool appearance score [53], weekly mean difficulty of passing stool score, and weekly percentage of volunteers who use auxiliary measures to assist with defecation (WPUAMA) will be evaluated each week from day 0 (week 0) to day 14 (week 2), day 28 (week 4), and day 42 (week 6). An SBM is defined as a bowel movement achieved without the use of any drugs or other auxiliary measures during the previous 24 hours [32, 54, 55] (Table 1).The Patient Assessment of Constipation Quality-of-Life (PAC-QOL) questionnaire (Appendix 5 [56, 57]) will be used to evaluate the QOL score on days 0, 14, 28, and 42.The Depression, Anxiety and Stress Questionnaire (DASS-21) [58, 59] (Appendix 6) will be completed online on days 0 (baseline), 14, 28, and 42 and used to assess the participants' emotional status (depression, anxiety, and stress) within the past week (Table 1).For the indicator of the gut microbiome, DNA will be extracted from the stool samples with the QIAamp Fast DNA Stool Mini Kit (Qiagen, Hilden, Germany) according to the manufacturer's instructions, and the quality of DNA will be examined using agarose gel electrophoresis and a NanoDrop spectrophotometer. Shotgun metagenomic sequencing will be performed on all samples using an Illumina HiSeq 2500 instrument. Libraries will be constructed from DNA fragments with a length of ∼300 bp; paired-end reads will be generated by sequencing 150 bp in the forward and reverse directions. Meanwhile, the metagenomic analysis will include several parts: the analysis of alpha diversity and beta diversity in each group to understand whether the differences in the microbiota compositions of groups are significant and a comparison of the taxonomic characteristics of the study group and the control group at the level of phylum, genus, and species to identify specific genes related to the individual differences of constipation. Metagenomic biological pathway analysis will be used to evaluate the effect of probiotics on the function of gut metagenomics in patients with constipation and to explore the metagenomic biological pathways contributing to the mechanism underlying the effect of probiotics on the treatment of constipation.For the indicator of the faecal metabolome, stool samples will be extracted using the protein precipitation method, and the supernatant will be transferred to sample vials for LC-MS/MS analysis. The original data will be subjected to peak alignment, retention time correction, and peak area extraction using the XCMS-Plus program. The structure of metabolites will be identified by accurate mass matching (<5 ppm) and two-level spectrum matching, and the METLIN database will be retrieved. We will then delete data with missing values > 50% in the group, normalize the data, and conduct multidimensional statistical analysis, including unsupervised principal component analysis (PCA), supervised partial least squares discriminant analysis (PLS-DA), and potential differentially abundant metabolite analysis. The metabolomic analysis might further identify the potential differentially abundant metabolites of probiotics in the treatment of constipation, and a correlation analysis between the gut microbiota and metabolites will be performed.

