### 2.14. Data Collection and Collation

The defecation diary (Figure 2) completed by the volunteers will be collected online daily, and the DASS-21 (Appendix 6) will be collected online as scheduled (see Table 1). One stool sample for the gut microbiome analysis and one for the metabolomics test will be collected from each volunteer on days 0 (preadministration period), 28 (administration period), and 42 (postadministration period); these samples will be stored separately and sent for tests at a temperature of −80°C in a special stool storage kit from Guangdong Longsee Company (https://www.longseemed.com).

An independent data management team (DMT) will be established to maintain and monitor study quality and safety. The data of individual characteristics, defecation diary entries (Figure 2), and DASS-21 data (Appendix 6) completed online by volunteers will be downloaded as Excel spreadsheets for further analysis. The gut microbiome and metabolomic data from stool samples will be examined by the Key Laboratory of Dairy Biotechnology and Engineering, Ministry of Education. All data will be submitted to the DMT for management and monitoring. The DMT will promptly analyse the data and contact collectors to resolve any uncertainty that occurs. All records that contain names or other personal information that could identify a participant, such as ID number or consent forms, will be stored separately from the study records. The database will be password protected by the DMT. The team will also have the authority to conduct an interim analysis or terminate the study's next step if the following situations occur: (1) if the probiotic does not affect the gut microbiome, then the study team will not conduct tests on the faecal metabolomes; and (2) if any severe adverse events related to the probiotics occur, the DMT will suggest terminating the study.

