In addition, the statistical analyses of metagenomic and metabolomic data will be performed using *R* software (v.4.0.2) and Adobe Illustrator. PCA and PLS-DA will be performed and visualized using the *R* packages vegan, ggplot, and ggpubr, and the adonis *P* value will be generated based on 999 permutations. The *t*-test, Wilcoxon test, and Kruskal–Wallis test will be used to evaluate differences in variables between and within groups; *P* values will be corrected for multiple testing using the Benjamini–Hochberg procedure. Meanwhile, Pearson's and Spearman's correlation coefficients will be calculated to analyse the correlations between different indicators in clinical, metagenomic, and metabolomic data.

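### The named between-arm microbiome and metabolome tests specify no use of each volunteer's own day-0 sample, so precision is lost to the extent that visits correlate

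*Protocol article*

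**What the plan says.** Section 2.14 of the protocol article states that stool for the microbiome and for the metabolome "will be collected from each volunteer on days 0 (preadministration period), 28 (administration period), and 42 (postadministration period". Table 1 shows the same three visits.

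For taxa, Section 2.9 plans "a comparison of the taxonomic characteristics of the study group and the control group at the level of phylum, genus, and species". Diversity is handled in the same section by "the analysis of alpha diversity and beta diversity in each group to understand whether the differences in the microbiota compositions of groups are significant". For the metabolome it lists "unsupervised principal component analysis (PCA), supervised partial least squares discriminant analysis (PLS-DA), and potential differentially abundant metabolite analysis".

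Section 2.15 then names the tests: "The *t*-test, Wilcoxon test, and Kruskal–Wallis test will be used to evaluate differences in variables between and within groups". For the multivariate comparison, "the adonis *P* value will be generated based on 999 permutations". On multiplicity, P "values will be corrected for multiple testing using the Benjamini–Hochberg procedure".

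None of these sentences mentions a day-0 covariate, a change score, a pairing of a volunteer's samples, or permutation by volunteer. Sections 2.8 and 2.9 do speak of changes from day 0, but that wording is attached to the diary outcomes.

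**The concern.** Only the comparison between arms at days 28 and 42 gives randomised evidence on the flora and metabolites. The within-arm comparisons over time have no placebo contrast. If the between-arm tests use post-treatment values alone, they carry the full spread between people, including the part that the day-0 sample could have explained.

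Two features of the plan give this some weight. First, the Discussion states the trial's hypothesis as P9 improving symptoms and quality of life by modifying the intestinal flora, so the flora contrast is the randomised test of that link. Second, Section 2.14 provides that the metabolome will not be tested if the probiotic is found not to affect the microbiome. A false-negative microbiome result could therefore cancel a listed secondary outcome.

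**Working it through.** **The plan's own figure.** Section 2.12 assumes a CSBM difference of 3 per week, SD 6, α = 0.05 (taken as two-sided) and 80% power. Per group, n = 2 × (6/3)² × (1.960 + 0.842)² ≈ 62.8, so 63, as stated. This concerns the primary outcome only. The article gives no effect size, variance or power for any stool-sample outcome.

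**Inputs for the check.**
- 100 per arm (Section 2.12), and 80 per arm if the full 20% drop out.
- r, the correlation between a volunteer's day-0 and later value on the analysis scale. It is not in the documents and is assumed to lie between 0.3 and 0.8.
- A true shift of 0.4 SD, assumed for illustration.
- Two-sided 0.05 per feature, before Benjamini–Hochberg. The correction will usually make the working threshold stricter and lower all the power figures; the variance ratios do not change.

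**Formulas.** Relative to a post-only comparison (variance 1), with equal variance at both visits:
- day 0 as covariate: 1 − r²
- change from day 0: 2(1 − r)
- shift detectable with 80% power: (1.960 + 0.842) × √(2(1 − r²)/n)
- power at shift d: Φ(d/√(2(1 − r²)/n) − 1.960)

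**Results.** The r = 0 row is the post-only test.

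| r | Variance, covariate | Variance, change | Post-only n/arm equal to 100 adjusted | Detectable shift, n = 100 (SD) | Detectable shift, n = 80 (SD) | Power at 0.4 SD, n = 100 | Power at 0.4 SD, n = 80 |
|---|---|---|---|---|---|---|---|
| 0 (post-only) | 1.00 | – | 100 | 0.396 | 0.443 | 81% | 72% |
| 0.3 | 0.91 | 1.40 | 110 | 0.378 | 0.423 | 84% | 76% |
| 0.5 | 0.75 | 1.00 | 133 | 0.343 | 0.384 | 90% | 83% |
| 0.7 | 0.51 | 0.60 | 196 | 0.283 | 0.316 | 98% | 94% |
| 0.8 | 0.36 | 0.40 | 278 | 0.238 | 0.266 | >99% | 99% |

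The variance cut is thus 9%, 25%, 51% and 64%. The covariate form is never worse than change, because 2(1 − r) − (1 − r²) = (1 − r)² ≥ 0. Change beats post-only only when r exceeds 0.5.

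**Multivariate test.** A simulated Euclidean version of the adonis test used 80 per arm, 50 features, a 0.1 SD shift in each, 300 runs and 199 permutations. Power for post-only / change / day-0-adjusted was:
- r = 0.3: 53 / 32 / 55%
- r = 0.5: 57 / 50 / 72%
- r = 0.7: 58 / 85 / 92%
- r = 0.8: 56 / 98 / 99%

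With no true shift, the post-only test rejected in 3% to 5% of runs, so it holds its level.

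**The case against.** The article is silent rather than explicit. It does not say whether the tested variable is a raw day-28 value or a change from day 0, and a t-test or Wilcoxon test on changes would fit the wording. The article is condensed, a separate analysis plan may exist, and these are secondary, mechanistic outcomes. The sentence on taxa also goes on to an exploratory aim about genes linked to individual differences. All of this is fair and limits the weight of the point. It does not remove it: the article goes as far as naming the tests, none is tied to day 0 in the arm comparison, and a plain change score would be a worse choice than a covariate at every r below 1.

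Three stronger readings are tempting, and the documents do not support them:
- *Person-to-person differences swamp the product effect.* No stool-outcome effect size, SD or correlation is given. The loss could be as small as 9% of variance at r = 0.3.
- *A chance day-0 imbalance will produce false product effects.* Allocation is randomised, and the nominal error rate already covers chance imbalance. The simulation agrees.
- *The day-0 samples go unused.* They enter the within-group tests, and the Abstract schedules every outcome at day 0 for comparisons both between and within groups. What is missing is a stated role in the arm contrast.

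**Conclusion.** The point holds as a loss of efficiency. The named between-arm microbiome and metabolome tests are valid, but they specify no use of a day-0 sample planned for every volunteer. Over an assumed r of 0.3 to 0.8, adjustment would cut variance by 9% to 64%, equivalent to 1.10 to 2.78 times as many volunteers. With 80 per arm and an assumed 0.4 SD shift, power at 0.05 would rise from 72% to between 76% and 99%.

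These figures rest on the assumed r and shift, on a roughly linear relation between visits on the analysis scale, and on reading the named tests as post-treatment comparisons. The primary outcome and its sample size are not touched. The change is worth making because the flora contrast carries the stated mechanism and may decide whether the metabolome is tested at all.

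**What to change.** State in Sections 2.9 and 2.15 that each between-arm test of a taxon, pathway, diversity index or metabolite at days 28 and 42 is a linear or rank ANCOVA on arm plus the volunteer's day-0 value. A log or centred-log-ratio scale is suitable for abundances. Keep the Benjamini–Hochberg correction. Do not substitute a plain change score.

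For beta diversity, test the arm-by-visit term by permuting arm labels at volunteer level, keeping each volunteer's samples together. Alternatively, compare within-volunteer distances (day 0 to 28, day 0 to 42) between arms. The arm-by-visit term behaves like a comparison of changes, so its gain also depends on r exceeding about 0.5. Reporting the day-specific adonis result beside it covers the case of low r.

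The cost is wording, plus a simple rule for a missing or unusable day-0 sample, such as imputing the baseline mean. No extra samples or visits are needed. The Trial Status section reports 130 of the planned 200 enrolled and recruitment continuing, so at that stage the wording could still be set before the final analysis.

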
### 2.10. Safety Evaluation

All related clinical trials have reported that probiotics are safe and do not induce significant adverse events compared with the placebo group. However, four types of adverse reactions related to probiotics should be considered, including symptoms that may be attributed to systemic infections, deleterious metabolic activities, excessive immune stimulation, and gastrointestinal side effects [60], which will be collected as possible adverse events during the study. Severe adverse events are those adverse events leading to study withdrawal, e.g., hospitalization, disability, mortal danger, or death. All adverse events, including symptoms, time of onset, duration, causal relationship to interventions, and measures taken, will be accurately recorded during the study. Any serious adverse events will be recorded along with the corresponding criteria and emergency measures and will be promptly reported to the Medical Ethics Committee of the First Affiliated Hospital of Nanchang University within 24 hours; a separate study report will be prepared. Based on the adverse events observed during the study, the safety of the probiotics will be evaluated as excellent (safe, without any adverse events), good (relatively safe with moderate adverse events that resolve on their own without any specific treatment and do not result in study withdrawal), conditional (adverse events that resolve after certain measures are taken and allow continued participation in the study), or unsafe (adverse events that result in study withdrawal) [61].

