### 2.6. Study Interventions

The *L. plantarum* P9 and placebo powders will be manufactured in parallel and independently by Research and Development Department, Jiangzhong Pharmaceutical Company Limited (Nanchang, China). Briefly, the preparation procedure consists of three steps: weighing, mixing, and packaging. *L. plantarum* P9 powder is composed of 20% maltodextrin, 20% orange powder, 20% maltitol, and 40% *L. plantarum* P9, while placebo powder consists of 60% maltodextrin, 20% orange powder, and 20% maltitol. Raw materials for *L. plantarum* P9 and placebo powders are mixed using a Hopper mixer (hit-400) and sealed into 2 g packages. The temperature is controlled at 25 ± 2°C, and the relative humidity is less than 65% during the three steps. In the study, when the product of *L. plantarum* P9 powder is manufactured, a randomized sample is sent to Jinhua Yinhe Biotechnology Co., Ltd. (https://yinhewdy168.foodmate.net/) for quality inspection. The activity of probiotics is greater than 67 billion colony-forming units (CFUs)/g.

The study will include three phases (Table 1), including a screening period (an observation period prior to treatment administration), an observation period during administration, and an observation period after administration. The interventions in each phase will be administered as follows:Period of screening (preadministration observation period) (days 14 to 0): in this phase, volunteers will not receive the intended interventions, i.e., probiotics and placebo. Eligibility screening will be performed as described during volunteer recruitment (Table 1).Observation period during administration (days 0 to 28): (1) Probiotics group: volunteers will take 1 package of *L. plantarum* P9 powder directly or with warm water (below 40°C) on a full stomach at a dose of 100 billion CFUs per day; if antibiotics must be taken, probiotics should be taken 2 hours later. (2) Placebo group: volunteers will take the placebo in the same manner as the probiotics group. The placebo contains no probiotics but has the same appearance, packaging, and taste as the *L. plantarum* P9 powder.All remaining probiotics or placebo (unused) and empty (used) packages will be collected at the end of this period to monitor compliance. During the study, both probiotics and placebo will be stored in a cool, dry place away from direct sunlight.Postadministration observation period (days 29 to 42): no probiotics or placebo will be taken.

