### 2.13. Compliance Monitoring and Withdrawal

The probiotics and placebo will be supplied as packages distributed in boxes. At the start of the administration period, the appropriate number of probiotic and placebo packages will be distributed to the participants. All used (empty) and unused packaging will be kept by volunteers. At the end of the administration period, these packages will be collected to verify the number of remaining packages and calculate the dosing rate. A dosing rate ≥80% indicates good compliance. A WeChat group will be established for the participants to improve compliance. The study personnel will post messages in the WeChat group to remind participants to take the samples as scheduled and complete the questionnaire. In addition, each participant will receive a reward of 300 RMB once they complete the follow-up.

Volunteers will be withdrawn from the trial for the following reasons: (1) continuous adverse reactions involving systemic infections that cannot be resolved after certain measures are taken, deleterious metabolic activities, excessive immune stimulation, gene transfer, and gastrointestinal side effects, which may be attributed to probiotics [60]; and (2) patients can actively withdraw from the trial at any time for any reason, and subsequent treatment will not be affected.

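### 'Severe' adverse events are defined by study withdrawal, so a related hospitalization in a volunteer who stays in the study need not meet the termination clause

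*Protocol article*

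**What the plan says.** Section 2.10 (Safety Evaluation) defines one category of event: "Severe adverse events are those adverse events leading to study withdrawal, e.g., hospitalization, disability, mortal danger, or death". It then moves to a different word for reporting: "Any serious adverse events will be recorded along with the corresponding criteria and emergency measures", with a report to the ethics committee within 24 hours. Table 1 also lists 'serious' events (SAEs), at days 14, 28 and 42.

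The same section sets a four-level safety grade. The third level, 'conditional', covers events that settle once something is done about them and let the volunteer carry on. The lowest is worded "or unsafe (adverse events that result in study withdrawal".

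Section 2.14 (Data Collection and Collation) uses the first word. If a 'severe' event related to the probiotic occurs, the DMT will suggest ending the study.

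Section 2.13 (Compliance Monitoring and Withdrawal) gives two grounds for withdrawal. One begins "continuous adverse reactions involving systemic infections that cannot be resolved after certain measures are taken" and runs on to "gene transfer, and gastrointestinal side effects, which may be attributed to probiotics". The other is the volunteer's own decision: "patients can actively withdraw from the trial at any time for any reason, and subsequent treatment will not be affected".

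**The concern.** Whether a volunteer leaves a study and how badly that volunteer was harmed are separate facts. Section 2.10 uses the first to define 'severe', and section 2.14 hangs the termination suggestion on that definition. Two volunteers could have the same related hospitalization, and the clause could apply to the one who leaves and not to the one who stays. Section 2.13 leaves that decision largely to the volunteer.

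What is at stake is whether one safety clause operates on the right events. Safety is a stated aim of the trial, and the Discussion offers the protocol as guidance for similar studies, so the definition may be copied. The efficacy analysis is not involved.

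**Working it through.** No figure in the plan needs reproducing and no formula applies, so the check sets the provisions side by side and follows single events through them.

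**Which term drives which action**

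| Provision | Term used | Action |
|---|---|---|
| 2.10, definition | severe | defined by withdrawal, with outcomes as examples |
| 2.10, expedited report | serious | ethics committee within 24 hours |
| 2.14, termination clause | severe, and related | DMT suggests termination |
| Table 1 | serious (SAEs) | collected at days 14, 28 and 42 |

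**Event A: a related hospitalization that resolves, with the volunteer staying in.**
1. Withdrawal (2.13). The first ground is about continuing reactions that may be attributed to probiotics. A hospitalization that resolves is not named there. The second ground is the volunteer's choice, which here is to stay. So there is no withdrawal.
2. Definition (2.10). With no withdrawal, the stated criterion for 'severe' is not met.
3. Grade (2.10). The event settled after measures were taken and the volunteer continued, which fits 'conditional' and not 'unsafe'.
4. Termination clause (2.14). The event is not 'severe' as written, so the clause need not apply.

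**Event B: the same hospitalization, with the volunteer leaving because of it.** Withdrawal occurs, the event is 'severe', the grade is 'unsafe' and the clause applies. The harm is the same as in A; only the decision to leave differs.

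**Event C: a continuing gastrointestinal reaction attributed to the probiotic, leading to withdrawal, with none of the four listed outcomes.** It is 'severe' as written and meets the clause. This errs toward caution, and it matters mainly for the fix, which must not lose these events.

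**Event D: a related death.** Participation ends, so every reading agrees.

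**Is the withdrawal-based reading forced?** It follows the grammar of the sentence, and the grading scale points the same way: the line between its two lowest levels is continued participation against withdrawal. Withdrawal is thus used as the measure twice in one section.

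**Can event A arise late in the trial?** Section 2.6 says: "Postadministration observation period (days 29 to 42): no probiotics or placebo will be taken". Table 1 still collects serious events at day 42, so an outcome-based definition should run to day 42.

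**The case against.** The strongest reply is that the four listed outcomes are the usual serious ones, so most readers would class any hospitalization as severe whether or not the volunteer left, and would treat the two words as loose synonyms. The sentence allows that reading. It does not remove the problem, because the stated criterion is still withdrawal and the grading scale repeats it.

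The second reply is that safeguards exist. Section 2.10 says: "All adverse events, including symptoms, time of onset, duration, causal relationship to interventions, and measures taken, will be accurately recorded during the study". Section 2.14 sends all data to an independent DMT charged with monitoring safety. A related hospitalization would reach that team on any reading, and the clause only has it suggest termination. This stands and limits the consequence.

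A reader might go further and infer any of the following, but the documents do not support it:
- *That the 24-hour report can lapse for event A.* This needs 'serious' to mean 'severe' and the listed examples not to be sufficient in themselves. Section 2.10 mentions corresponding criteria for serious events, and the full protocol, which is not shown, may set them out.
- *That safety will be judged without comparison with placebo.* The article does not describe that comparison alongside the grade, but such detail is commonly left to the full protocol or analysis plan.
- *That information is missing for volunteers already enrolled.* The list of recorded items is not exhaustive, measures taken can capture a hospital stay, and serious events are recorded with their criteria. No gap is shown.

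**Conclusion.** The point holds as a minor error of safety wording. Section 2.10 states a definition based on withdrawal, and section 2.14 attaches a safety action to it. As written, a related hospitalization in a volunteer who stays in need not meet the termination clause. Because the definition is stated and used, this is more than detail left to a fuller document.

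The conclusion assumes that the sentence in 2.10 is applied as worded and that the full protocol contains no overriding definition of 'severe'. On the generous reading the practical consequence disappears, though the inconsistent terms remain. The documents give no adverse event rate, so how many events would be mis-sorted cannot be derived. The article does not show that a hospitalization would go unseen: it would be recorded and would reach the DMT. What is uncertain is only whether the clause obliges the team to suggest termination.

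**What to change.** In section 2.10, replace the definition with one based on outcome: a serious adverse event is any adverse event that results in death, mortal danger, hospitalization or disability, whether or not the volunteer withdraws, from the start of administration through day 42. Use that term for the 24-hour report and in the section 2.14 clause. Table 1 already says 'serious' and needs no change.

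Add to section 2.14 that any withdrawal due to a related adverse event goes to the DMT for separate review. Without this, events such as C above would drop out of the clause with nothing in their place.

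The cost is amendment wording in 2.10 and 2.14 and ethics committee approval. The trade-off is that related withdrawals with none of the four outcomes no longer prompt a termination suggestion by definition, which is why the separate review has to be written in. Sample size and efficacy analysis do not change.
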